### Sample size {14}

The required sample size was calculated based on the effect size (Cohen’s *d*) from previous research [30, 67, 68]. Since the effect size varies between 0.3 and 0.83, a conservative assumption is made with a small effect size of 0.3, *α* of 0.05, and *ß* of 0.8. Since numerous studies provide evidence that DAs significantly reduce decisional conflict [30, 38, 69], a superiority study with a one-sided *t-*test is conducted. Using the one-sided *t-*test, a sample size of 139 patients per group is required. Assuming an average drop-out rate of 10% of *BRCA1/2* mutation carriers in previous evaluation studies [31, 32, 34, 69, 70], the planned sample size is *n* = 155 participants per group, yielding a total of 310 required participants.

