### Trial design {8}

The trial is designed as a monocentric randomised controlled parallel-group superiority trial with a 1:1 allocation ratio.

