## Statistical methods

### Analysing primary and secondary outcomes {20a}

Analysis of the baseline data (t0) will be done to ensure the comparability of the two study groups. Outcomes are measured at t1 and t2. All primary and secondary effectiveness variables will be described by statistical characteristics values. Continuous data will be described by mean, standard deviation, median, minimum and maximum. Categorical data will be described by using frequencies and percentages. The number of non-missing values will also be given.

The primary outcome at t1 is decisional conflict. The mean differences of the primary outcome between both groups will be compared using the independent *t-*test in case of normal distribution. In addition, the mean differences in the score within the groups between t0 and t1 will be compared using a dependent *t-*test. Non-parametric tests will be used in case of non-normal distribution. Secondary outcomes comprise the mean differences in scores of the stage of decision-making, stress, anxiety and depressive symptoms between t0, t1 and t2. A further secondary outcome measured at t2 is the regret of the decision. For these analyses, a dependent respectively independent *t-*test will be used in case of normal distribution, non-parametric tests will be used in case of non-normal distribution. Data will be analysed by using IBM SPSS Statistics for Windows, version 27.0 (IBM Corp: Armonk, NY) and R [71]. An alpha level of 0.05 is considered significant in all statistical tests.

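### The primary test is prespecified as one-sided at 0.05 only because earlier trials were positive; the 80% power belongs to that test alone (about 70% two-sided), the analysis section does not restate the side, and ß is misstated

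*Protocol article*

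**What the plan says.** Sample size {14} takes Cohen's d from earlier studies ("Since the effect size varies between 0.3 and 0.83"), and "a conservative assumption is made with a small effect size of 0.3". It sets α at 0.05 and ß at 0.8. It then moves from "Since numerous studies provide evidence that DAs significantly reduce decisional conflict" to the statement that "a superiority study with a one-sided *t-*test is conducted". The result is that "a sample size of 139 patients per group is required", raised to 155 per group and 310 in total for 10% drop-out. Trial design {8} describes a "randomised controlled parallel-group superiority trial with a 1:1 allocation ratio".

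Analysing primary and secondary outcomes {20a} compares the groups on the primary outcome with an independent t-test, or a non-parametric test if the data are not normal. It adds: "An alpha level of 0.05 is considered significant in all statistical tests". No side is given there, and no baseline covariate is named. Under Outcomes {12}, the primary outcome is the change in DCS at 3 months, and the scale is administered at t0, t1 and t2.

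**The concern.** Positive earlier trials make a benefit likely. They do not make a 5% one-sided error rate appropriate, and they do not make the opposite direction uninteresting. Two consequences follow.

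- **Evidential bar.** The chance of declaring a benefit when there is none is 5%, against 2.5% for the favourable tail of a two-sided 5% test. The Discussion says that the decision aids will be integrated into the centres' care after the evaluation, so the standard of proof matters.
- **Unfavourable direction.** A one-sided test cannot declare that a decision aid raises decisional conflict. The protocol has no specific plan for collecting unintended effects (section {22}) and no independent monitoring committee (section {21a}), so the questionnaire scores are the main place where such an effect would show.

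The side is also not repeated where the tests are specified. The single sentence on alpha covers between-group, within-group and secondary comparisons. Section {54}-type subgroup comparisons with chi-square or Fisher tests are planned as well under Additional analyses {20b}. These cannot all sensibly be one-sided in favour of the decision aid, so for everything except the primary test the side is open.

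Finally, ß is by convention the type II error. Read literally, ß of 0.8 means a trial with 20% power.

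**Working it through.** **Inputs.** From Sample size {14}: d = 0.3 (SD = 1), α = 0.05 one-sided, power 0.8 (printed as ß), drop-out 10%. From Trial design {8}: 1:1 allocation. Powers use the noncentral t distribution with 2n − 2 degrees of freedom and noncentrality d / √(2/n).

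**1. Reproduce the plan's figure.** One-sided 0.05, power 0.8, d = 0.3: n = 138.07, rounded up to 139 per group (power 80.2%). Drop-out: 139 / 0.9 = 154.4, rounded up to 155; 2 × 155 = 310. All three figures reproduce.

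**2. Read ß literally.** Power of 0.2 with the same inputs needs only about 16 per group. The 139 follows only from power 0.8, so the number is right and the label is wrong.

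**3. Same sample, two-sided 0.05.**

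| Quantity (d = 0.3, unadjusted) | One-sided 0.05 | Two-sided 0.05 |
|---|---|---|
| Power, 139 per group | 80.2% | 70.3% |
| Power, all 155 per group evaluable | 83.9% | 74.9% |
| n per group for 80% power | 139 | 176 |

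At 139 per group, the effect detectable with 80% power two-sided is d = 0.337.

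**4. Where the side decides the result.** Standard error of the difference in SD units: √(2/139) = 0.120. Smallest significant observed effect: 1.650 × 0.120 = 0.198 one-sided and 1.969 × 0.120 = 0.236 two-sided. If the true d is 0.3, the observed effect falls between the two with probability about 10% (80.2% − 70.3% = 9.9%).

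**5. What baseline adjustment could return.** The documents give no t0–t1 correlation r for the DCS, so r is an assumption. They also do not say whether d = 0.3 is in SDs of the follow-up score or of the change score. With equal SDs at t0 and t1, ANCOVA on the t1 score has residual SD √(1 − r²) times the follow-up SD, and the change score has SD √(2(1 − r)) times the follow-up SD. The effective standardised effect is therefore

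- 0.3 / √(1 − r²) if d is in follow-up SDs;
- 0.3 × √(2 / (1 + r)) if d is in change-score SDs.

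| r (assumed) | Effective d, follow-up SDs | Two-sided power | Effective d, change SDs | Two-sided power |
|---|---|---|---|---|
| 0.3 | 0.314 | 74% | 0.372 | 87% |
| 0.5 | 0.346 | 82% | 0.346 | 82% |
| 0.7 | 0.420 | 94% | 0.325 | 77% |

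Over this range the adjusted two-sided power is above the unadjusted 70.3% on either reading, but the two readings trend in opposite directions as r rises and agree only at r = 0.5.

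**The case against.** The strongest reply is that the protocol chose its test openly. Sample size {14} says that a one-sided test is conducted, the Objectives state a directional hypothesis, and the nominal error rate is the declared 5%. Three stronger readings are tempting, and the documents support none of them.

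- **That the two sections contradict each other.** They do not. The analysis section never says two-sided, and 0.05 with an independent t-test is compatible with a one-sided test. For the primary outcome, the sample size section settles the side. What is open is the side of the other tests.
- **That the sample size is wrong or the trial misses its stated power.** It does not. The protocol claims 80% for a one-sided test, and that is correct. The 70% describes a test that the protocol did not choose. It shows what the chosen side is worth, not an error of calculation.
- **That ANCOVA restores power to a known 82%.** That figure holds only at an assumed r of 0.5. The range is 74% to 94% or 77% to 87%, depending on the SD unit.

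It can also be said that recruitment closed on 30 September 2021, so that a new model is a late change to a prespecified analysis. This stands as a condition on timing. Likewise, the ß entry is a slip of notation with no effect on the 139; it is still a wrong figure as printed.

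What the reply does not answer is the justification. Disclosing a one-sided 5% level does not supply a reason for it, and superiority can equally be tested two-sided.

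**Conclusion.** The point holds as a weakly justified design choice with two smaller defects. The one-sided 0.05 level rests only on the expected direction. It doubles the false-positive rate for benefit relative to a two-sided 5% test and leaves harm untestable in the primary analysis. Measured on the planned 139 evaluable women per group at d = 0.3 without adjustment, the choice of side is worth about 10 percentage points of power (80.2% against 70.3%), or 37 women per group (176 − 139). The smaller defects are the missing side for the remaining tests and the mislabelled ß. The planned t-test also leaves unused, as a covariate, a baseline score that the trial already collects.

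These figures rest on the protocol's own d, 10% drop-out and a t-test on roughly normal data. The ANCOVA powers rest in addition on an assumed correlation, equal SDs at the two times and an assumed SD unit for d.

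**What to change.** Before the analyst is unblinded, and in a dated amendment because the rest of the research team knows the allocation:

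1. Analyse the primary outcome by ANCOVA of the t1 DCS score on group and t0 DCS score, with a two-sided test at 0.05 and a two-sided 95% confidence interval.
2. In section {20a}, state the side of the primary test and of the secondary, within-group and subgroup tests.
3. In section {14}, disclose that 139 per group at d = 0.3 gives 80% power one-sided but about 70% two-sided without adjustment. Give no single ANCOVA power. If one is wanted, label it an assumption and show the range: for r = 0.3 / 0.5 / 0.7, 74 / 82 / 94% with d in follow-up SDs, or 87 / 82 / 77% with d in change-score SDs.
4. Replace the ß entry by power 0.8 (ß 0.2).

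This needs no further patients and no new data, since the DCS is already collected at t0 and t1. The cost is an amended text, a changed primary model that must be fixed before results are known, and a less favourable power statement.

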### Recruitment {15}

The following strategies are used to achieve adequate participant enrolment to reach the target sample size: Posters are placed in the waiting room areas of the recruitment centre to publicise the study and invite interested women to participate. A study nurse will check women’s files who have upcoming appointments in the recruiting institution and screen these for eligibility. Then, counselling physicians are requested to actively approach eligible women after post-test genetic counselling or during an appointment for the intensified breast cancer screening (and aftercare) programme.

#### Allocation: sequence generation {16a}

Study participants will be randomly assigned to either IG or CG with a 1:1 allocation. Sequence generation is done with a computerised random number generator by a member of the research team who is not involved in data analysis.

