### Intervention

Once the completed baseline questionnaires (t0) have been returned to the data evaluation institution, the DAs will be sent by regular mail to those participants randomised to the IG with a request to use the DA for information and decision support at home. Previvors will receive DA-A, and survivors will receive DA-B.

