#### Allocation concealment mechanism {16b}

After sequence generation, a member of the research team prepares the enrolment packages that contain the study documents for eligible participants. There are no differences in the enrolment packages between IG and CG. Thus, all packages look exactly the same and contain the same documents. Each package is marked with a study ID. Only the members of the research team at the data evaluation institution know the allocation of the study IDs to IG and CG. The participants, the recruiting physicians and the study nurse will not be able to decode the allocation.

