#### Implementation {16c}

The enrolment packages are prepared and equipped with a study ID by the data evaluation institution and then transferred to the recruitment institution. After informed consent, the recruiting physicians enrol eligible women into the study, and each participant receives an enrolment package. As the allocation to IG or CG is determined by the study ID, both physicians and participants are blinded regarding the assignment of the participants to IG or CG.

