### Additional analyses {20b}

Subgroup analyses are planned to investigate whether there are differences in primary and secondary outcomes (1) between *BRCA1/2* mutation carriers without a personal history of cancer and those with a personal history of unilateral BC and (2) between women recruited directly after the post-test genetic counselling or later on at an appointment as part of an examination for the intensified breast cancer screening (and aftercare) programme. Subgroup analyses will be performed using the independent *t-*test for normally distributed metric variables, and non-parametric tests will be used in case of non-normal distributions. The chi-square test or Fisher’s exact test will be used for categorical variables. Beyond group allocation, demographic data will be used as the independent variable.

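### No stratification by cancer history or recruitment route is named, and the primary test has no covariates, so chance imbalance in these factors enters the primary estimate unadjusted

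*Protocol article*

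**What the plan says.** Allocation is set out in three consecutive sections of the protocol article.

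- Allocation: sequence generation {16a}: "Study participants will be randomly assigned to either IG or CG with a 1:1 allocation". On the method: "Sequence generation is done with a computerised random number generator by a member of the research team". No stratification factor and no blocking is named.
- Allocation concealment mechanism {16b}: packages are made up after the sequence exists, and "all packages look exactly the same and contain the same documents".
- Implementation {16c}: "As the allocation to IG or CG is determined by the study ID, both physicians and participants are blinded". The physician hands over a package after consent.

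Two features of the participants are known at that moment. Eligibility criteria {10} admits women without cancer (A) and women with unilateral breast cancer (B). Enrolment and randomisation gives two routes: directly after counselling, or at a later screening or aftercare visit. Cancer history first plays a part after allocation, when the aid is posted: "Previvors will receive DA-A, and survivors will receive DA-B".

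Additional analyses {20b} takes these two features as its subgroup factors. The first compares carriers "without a personal history of cancer and those with a personal history of unilateral BC"; the second compares the two routes.

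Analysing primary and secondary outcomes {20a} compares the arms on decisional conflict at t1 with an independent t-test, or a non-parametric test if the data are not normal. Neither is given a covariate.

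**The concern.** The article itself gives reasons to expect both factors to bear on the primary outcome. Background and rationale {6a} describes survivors' decisions as potentially more complex because of competing risks. Eligibility criteria {10} describes the later-route women as having already opted for screening for the time being, so they stand at a different stage from women who have just been counselled.

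When a factor is related to the outcome, is known at enrolment and is used neither in the allocation nor in the primary model, any chance difference in its share between the arms becomes part of the estimated treatment effect. At stake is avoidable error in the one estimate on which the trial is judged. To a lesser degree, arm sizes may also be uneven within the smaller population.

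**Working it through.** **Inputs.** Sample size {14}: d = 0.3, α = 0.05 one-sided, 139 evaluable and 155 randomised per arm, 10% dropout, 310 in total. The 0.8 printed there as β reproduces the sample size only when read as power. The shares of survivors and of later-route women are not given and are assumed below. The outcome difference between the groups is also assumed, at 0.2 to 0.5 SD.

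**1. The plan's own figure.** The exact one-sided t-test solves to 138.07 per arm, rounded up to 139. Then 139 / 0.9 = 154.4, rounded up to 155, and 2 × 155 = 310. The figure reproduces, and nothing below changes it.

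**2. Chance imbalance between arms.** For a factor with share p and 155 per arm, the 95% range of the difference in share is ±1.96 × √(p(1 − p) × 2/155).

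- p = 0.3: 1.96 × √(0.21 × 2/155) = 1.96 × 0.0521 = 10.2 percentage points.
- p = 0.5: 1.96 × √(0.25 × 2/155) = 1.96 × 0.0568 = 11.1 percentage points.

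An exact (hypergeometric) calculation with arms fixed at 155 gives the chance of a difference of at least 10 points:

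| Assumed share | Chance of a difference of 10 points or more |
|---|---|
| 10% | 0.2% |
| 20% | 3.3% |
| 30% | 4.7% |
| 40% | 8.2% |
| 50% | 6.9% |

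If one factor has a 30% share, the other a 50% share and the two are independent, the chance that at least one reaches 10 points is 1 − 0.953 × 0.931, or about 11%.

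**3. Effect on the estimate.** Shift = difference in share × outcome difference between the groups.

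- 0.10 × 0.2 SD = 0.02 SD; 0.02 / 0.3 = 7% of the planned effect.
- 0.10 × 0.5 SD = 0.05 SD; 0.05 / 0.3 = 17% of the planned effect.

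The standard error of the comparison at 139 per arm is √(2/139) = 0.12 SD, so these shifts are about 0.17 and 0.42 of a standard error.

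**4. Arm sizes within the smaller population.** At an assumed 30% share there are 0.3 × 310 = 93 survivors. Under a simple 1:1 draw, the 95% range of the number in the intervention arm is 37 to 56. With arms fixed at 155 it is about 39 to 54. A 60:40 split keeps 4 × 0.6 × 0.4 = 96% of the information; one-sided power for d = 0.3 among 93 women is 41.0%, against 42.1% for an even split.

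**5. Overall power.** With 278 evaluable women, average power under simple randomisation is 80.3%, against 80.4% at exactly 139 per arm.

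**The case against.** The case for leaving the plan alone is substantial, and much of it stands.

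- **Validity.** Unstratified 1:1 allocation of 310 women at one centre is sound. Chance imbalance is already covered by the error rate of the t-test, and the shift in step 3 is under half a standard error even for an unlucky draw. This stands. The point concerns precision and conditional accuracy, not validity.
- **Change scores.** The Abstract and Outcomes {12} define the primary outcome as change in decisional conflict, and stable differences in level largely cancel in a change score. This stands in part: a difference in how the two groups change over three months does not cancel.
- **Other provisions.** Additional analyses {20b} says that demographic data will serve as an independent variable. That concerns the additional analyses, and neither cancer history nor route is a demographic variable. It does not alter the primary test.

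Three stronger readings are tempting, and the article does not support them.

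- A reader might infer that A and B draw from one common pool of packages. The article never says so. The sentence on identical packages compares intervention with control, and separate ID lists for A and B are not excluded. They may appear in the full protocol, which is not shown.
- A reader might infer that 1:1 balance is required within A and within B because each has its own aid. Objectives {7} sets a pooled hypothesis, and the Discussion explains why both aids can be evaluated in one trial. The within-population comparisons are additional analyses, and step 4 shows that a moderately uneven split costs them little.
- A reader might take the baseline look at 70 women in Interim analysis {21b} as the only safeguard. That look is exploratory, and {20a} separately plans a baseline comparison of the full groups. Neither, however, states what would follow if a difference were found.

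**Conclusion.** The point holds as a modest improvement to the analysis. The allocation as described names no stratification by cancer history or route, and the stated primary test cannot correct for a chance difference in either.

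Under the assumptions in the working, the consequence is an uncommon shift of 0.02 to 0.05 SD. These figures depend on shares and group differences that the article does not give; smaller shares or weaker relations to the outcome make the shift smaller. The documents give no ground for saying that the trial is biased, underpowered or wrongly randomised.

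The point does not depend on how the lists were really built. If they were unstratified, adjustment removes the chance imbalance. If the full protocol did stratify, the primary model should still contain the stratification factors.

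**What to change.** Trial status gives 30 September 2021 as the close of recruitment, so the allocation can no longer be changed. Before unblinded analysis:

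1. Prespecify the primary comparison of DCS at t1 as a linear model (ANCOVA) with arm, baseline DCS, cancer history (A or B) and recruitment route, in place of the unadjusted t-test. With baseline DCS in the model, the arm effect is the same whether the outcome is written as the t1 score or as change from t0.
2. Report arm sizes and baseline values within A and within B.
3. State whether the ID lists were stratified or blocked.

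The cost is a few lines of text. Cancer history and route are needed for the planned subgroup analyses in any case. Only women who returned the t0 questionnaire receive the one at t1, so apart from incomplete scales no t1 respondent lacks a baseline DCS. The sample size is unchanged.

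For a future trial of this kind, separate blocked ID series by cancer history would be the low-cost design choice. The series label would reveal the population but not the arm, so concealment would be kept.

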#### Allocation concealment mechanism {16b}

After sequence generation, a member of the research team prepares the enrolment packages that contain the study documents for eligible participants. There are no differences in the enrolment packages between IG and CG. Thus, all packages look exactly the same and contain the same documents. Each package is marked with a study ID. Only the members of the research team at the data evaluation institution know the allocation of the study IDs to IG and CG. The participants, the recruiting physicians and the study nurse will not be able to decode the allocation.

#### Implementation {16c}

The enrolment packages are prepared and equipped with a study ID by the data evaluation institution and then transferred to the recruitment institution. After informed consent, the recruiting physicians enrol eligible women into the study, and each participant receives an enrolment package. As the allocation to IG or CG is determined by the study ID, both physicians and participants are blinded regarding the assignment of the participants to IG or CG.

